#### Secondary outcomes

Pulmonary function (FVC): FVC will be measured through a spirometry test, the same as FEV1.

Quality of life (CFQ-R): Quality of life will be subjectively assessed by the Persian version of the Cystic Fibrosis Questionnaire-revised (CFQ-R) [43, 44]. This questionnaire examines different domains (physical functioning, vitality, emotional state, social functioning, role functioning of the individual, body image, eating disorders, treatment burden, general perception of health, respiratory, and digestive symptoms) affecting the quality of life of the person in the last 2 weeks and has been prepared in 3 versions according to the age of the patient. The differing versions are for:Children 6 to 13 years oldParents of above-aged childrenAdults 14 years old and older

The scale of answering questions is a 4-point scale. Total points are calculated and standardized in the range of 0 to 100. The closer the final score is to 100, the higher the quality of life. The MCID for the physical domain is 11.4 points increase, and for the respiratory domain, 7.3 has been calculated [36]. The validity and reliability of the Persian-translated version of the CFQ-R have been evaluated by Talebi et al. [43, 44]. The Cronbach-alpha for the CFQ-R was 0.65–0.91 for the children and parents versions, and ≥ 0.70 for the adult version, showing good internal consistency.

#### Other variables

In addition to the aforementioned outcomes, demographic and physiological variables such as age, sex, height, weight, medication history, physical activity level, and history of performing ACTs will be measured. These data will be reported as the baseline demographic information of the participants in Table 1 of the final paper, and they are balanced between the two groups by randomization method. There is no intention to do statistical analysis on these variables.

### Participant timeline {13}

Participant timeline is presented in Fig. 1 and study’s time schedule is presented in Table 3.

**Table 3 Tab3:**
[figure not shown]
Study’s time schedule

**Fig. 1 Fig1:**
[figure not shown]
Patient timeline

### Sample size {14}

The prevalence of CF disease is lower in the Asian continent [1] as reported as 1 per 100,000–350,000 in the Middle East and 1 per 100,000 in Iran [5]. Thus, the number of diagnosed CF patients is low. On the other hand, the coordinating center has dedicated the CF specialized clinic of the Children’s Medical Center Hospital to the trial team, for a limited short time frame. Considering these factors, we selected the randomized controlled trial study by Sosa et al. [45] which was closest to our trial in terms of methodology and variables, as the basis for sample size calculation. In this study, 22 participants, 11 in each group, were recruited. Adding a 30% drop-out rate probability to each group, we anticipate recruiting 15 participants in each trial arm. Using power analysis, the required sample size with a power of 0.8 and an α of 0.05, a total sample size of 30 children and adolescents is determined.

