### Objectives and hypotheses {7}

In this trial, we aim to include 30 children and adolescents of CF patients into a 1:1 randomized controlled trial study. We will compare the effects of conventional chest physiotherapy (CPT) and sham aerobic exercise in one group and aerobic exercise and sham CPT in the other group. The primary objective is to evaluate the effects of the 18-session aforementioned treatments on pulmonary function (FEV1) and functional capacity in children and adolescents with CF. The secondary objective is to assess the changes in sputum culture, pulmonary function (FVC), and quality of life of CF patients.

We hypothesize that there will be an increase by at least 7.1% in FEV1% percent predicted (minimally clinical important difference (MCID) considered for FEV1 [36]), a significant increase in the amount of FVC, at least 33-m increase in the distance covered in 6MWT (MCID considered for 6MWT [36]), a significant increase in the percentage of negative sputum culture tests and reduction of colony count tests after 6 weeks of aerobic exercise and CPT in CF patients, and a significant difference between the two groups. Also, the CFQ-R quality of life questionnaire score is expected to have a significant increase of at least 11.4 points in the physical domain, 7.3 points in the respiratory domain (MCIDs considered for CFQ-R [36]), and in the overall score.

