## Statistical methods

### Statistical methods for primary and secondary outcomes {20a}

Data will be analyzed using Stata version 16. The normal distribution of data will be analyzed by the Shapiro–Wilk test. If the distribution is normal, parametric tests will be used for analysis before and after the intervention. To determine the homogeneity of variances (i.e., variances approximately equal across groups), Levene’s test will be employed. If the variance is equal, the analysis of covariance (ANCOVA) will be used. The covariance variable in this test will be the initial data values before the intervention. The significance level of the tests is set at 0.05. In addition to the significance index, the effect size index is also used by Cohen’s *d* method to compare two treatment methods for each variable. Therefore, the effect of the intervention on each of the dependent variables is determined, regardless of the sample size. According to the new interpretation presented, the effect size can be divided and interpreted as follows: from 0.01 to 0.2, very small; from 0.2 to 0.5, small; from 0.5 to 0.8, moderate; from 0.8 to 1.2, large; from 1.2 to 2, very large; and more than 2, very large [46].

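### The stated 80% power for 30 children has no shown basis: the number equals another trial's recruitment plus 30%, and no outcome, difference, SD or test is given

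*Protocol article*

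**What the plan says.** Sample size {14} first explains the constraints: few diagnosed patients and limited access to the clinic. It then chooses one earlier randomised trial, "which was closest to our trial in terms of methodology and variables, as the basis for sample size calculation". What it reports from that trial is its size: "In this study, 22 participants, 11 in each group, were recruited". The drop-out step follows: "Adding a 30% drop-out rate probability to each group, we anticipate recruiting 15 participants in each trial arm". The last sentence of the section cites a power analysis, "the required sample size with a power of 0.8 and an α of 0.05", and concludes that "a total sample size of 30 children and adolescents is determined".

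The targets stand elsewhere. Objectives and hypotheses {7} says "We hypothesize that there will be an increase by at least 7.1% in FEV1% percent predicted", and at least 33 m on the 6MWT, in both cases as a rise after six weeks of treatment. For the comparison between the groups it expects only a significant difference. Outcomes {12} repeats 7.1% and 33 m as MCIDs. Statistical methods {20a} plans an ANCOVA on the baseline value and says "The significance level of the tests is set at 0.05", without stating sidedness. The same section labels a Cohen's d of 0.8 to 1.2 large and 1.2 to 2 very large.

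**The concern.** The section gives two origins for one number. The first, another trial's enrolment plus an allowance for drop-out, already yields 15 per arm, so the power analysis has no visible role. How many patients another study recruited says nothing about this trial's power for FEV1 or the 6MWT. A power of 0.8 has meaning only for a stated difference, SD and test, and none is given.

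The figure will be used when the result is read. The Discussion says that a significant difference can give one treatment clinical priority. If no difference is found, readers will take that as the result of a trial with 80% power, without knowing for which effect.

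**Working it through.** **Inputs from the protocol article.** 11 per group in the earlier trial, 30% drop-out, 15 per arm, power 0.8 and α 0.05 (Sample size {14}); 7.1 points and 33 m ({7} and {12}); ANCOVA on baseline ({20a}). Not given: outcome used for sizing, between-group difference, SD, baseline correlation, test, sidedness. I assume a two-sided test.

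**1. The plan's own figure.** 11 × (1 + 0.30) = 14.3, rounded up to 15 per arm, so 30 in total. This reproduces the stated number without any power calculation. The power step cannot be reproduced, because its inputs are not reported.

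**2. Drop-out arithmetic.** To keep 11 after 30% loss: 11 / (1 − 0.30) = 15.7, so 16 per arm. With 15 recruited, 15 × 0.70 = 10.5 remain. Fifteen per arm keeps 11 for a loss of up to 1 − 11/15 = 26.7%.

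**3. Detectable difference at 80% power.** Two-sample t-test (noncentral t), two-sided 5%, solved for the difference divided by the SD. For the ANCOVA, the SD in steps 3 and 4 is the residual (baseline-adjusted) SD. In raw-SD units the figure is multiplied by √(1 − r²), where r is the correlation of the outcome with baseline. For r = 0.7, an assumed value, √(1 − 0.49) = 0.714.

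| Analysed per arm | In adjusted SDs | In raw SDs if r = 0.7 |
|---|---|---|
| 15 | 1.06 | 0.76 |
| 11 | 1.26 | 0.90 |
| 10.5 | 1.29 | 0.92 |

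**4. Largest adjusted SD that still gives 80% power,** taking 7.1 points and 33 m as illustrative between-group differences.

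- 15 per arm: 7.1 / 1.060 = 6.7 points; 33 / 1.060 = 31 m.
- 11 per arm: 7.1 / 1.256 = 5.7 points; 33 / 1.256 = 26 m.

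**5. Power over a range of adjusted SDs.** All SDs here are assumptions, and favourable values are included.

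| Difference | Adjusted SD | Power, 15 per arm | Power, 11 per arm |
|---|---|---|---|
| 7.1 points | 5 | 96% | 89% |
| 7.1 points | 8 | 65% | 51% |
| 7.1 points | 10 | 47% | 35% |
| 7.1 points | 12 | 35% | 26% |
| 7.1 points | 15 | 24% | 18% |
| 33 m | 25 | 94% | 84% |
| 33 m | 40 | 59% | 45% |
| 33 m | 50 | 42% | 31% |
| 33 m | 60 | 31% | 23% |

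Power thus runs from well above 80% to below 25%, depending on an SD that the article does not state.

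**The case against.** The article is condensed and says that the earlier trial was the basis of the calculation. An effect size and SD may have been taken from it without being printed. That stands: one can show that the inputs are not reported, not that none existed. The remedy must therefore let the authors supply them. It does not rescue the text, which displays a derivation and then attaches a power to it that this derivation cannot produce.

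Several stronger readings are tempting, and the article does not support them.

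- That the plan misses its required 11 per arm. It never says that it needs 11, only that the earlier trial recruited 11 per group. The inflation slip is one patient per arm.
- That 15 per arm suffices only for a very large effect. On the article's own scale, 1.06 is large. Values above 1.2 arise only after the full 30% loss and in adjusted-SD units; in raw SDs the ANCOVA brings them to about 0.90 if r = 0.7.
- That the SDs needed for 80% power are implausibly small. The wide age and FEV1 eligibility range bears on the raw SD, whereas the limits in step 4 concern the adjusted SD. With assumed values, a raw SD of 15 points and r = 0.9 gives 15 × √(1 − 0.81) = 6.5, just inside the limit of 6.7 for 15 per arm; a raw SD of 20 gives 8.7, outside it.
- That the trial is underpowered for its own between-group targets. Objectives {7} sets 7.1 points and 33 m as increases after treatment, so their use as group differences is illustrative.

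The article is also open about the constraints. It cites low prevalence and limited clinic time, and lists the small sample as a limitation. That softens the point but does not retract the 80%. Multiple imputation ({20c}) means that the analysis need not be confined to completers, but it would recover little power for missing outcomes.

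**Conclusion.** The point holds as a fault in the stated derivation: 80% power is claimed for 30 children, while the only calculation shown is another trial's recruitment plus 30%. The claim cannot be checked and is unsupported as written. Whether true power lies above or below 80% cannot be determined from the article. Under a two-sided 5% t-type comparison it is 80% for about 1.06 adjusted SDs with 15 per arm and 1.26 to 1.29 with 10.5 to 11. These figures do not depend on an assumed SD; their translation into points, metres or raw SDs does. The drop-out slip is a minor remark.

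**What to change.** Rewrite the end of Sample size {14}:

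- Either give the outcome, between-group difference, SD, baseline correlation, test and sidedness that produce the stated power, or withdraw the sentence with the 0.8.
- State that 30 is the feasible number, for the reasons the section already gives.
- Correct the drop-out arithmetic: at 30% loss about 10 to 11 per arm are evaluable, and 16 per arm would be needed to keep 11.
- Report the detectable difference (about 1.06 adjusted SDs with 15 per arm, 1.26 to 1.29 with 10.5 to 11), and the power for chosen between-group differences over a stated SD range that includes favourable values.

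The cost is one paragraph in the protocol and the same correction in the final paper. No additional children need be enrolled. The downside is that the stated power will probably look less favourable.

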### Recruitment {15}

In order to reach the target sample size, the pediatric pulmonologist from the CF specialized clinic will refer patients diagnosed with CF to the rehabilitation clinic of the Children’s Medical Center Hospital. The treatment course will be explained to the patients and their parents and they are encouraged to participate. Patients who are willing will enter the study based on the eligibility criteria. In addition, patients will be called among the previous files available at the center.

## Assignment of interventions: allocation

### Sequence generation {16a}

Participants will be randomly allocated to intervention groups A and B, in a 1:1 ratio, using block balanced randomization method.

### Allocation concealment {16b}

The randomization process was done by a statistician ([name]) before the start of the study. After the initial evaluation of participants by the examiner, who has enough experience and knowledge to do it, sealed numbered envelopes, corresponding to the sequential number of each person entered into the study, will be presented and the therapeutic intervention will be adjusted based on the letters inside the envelopes. The examiner and participants will be unaware of the letters inside the envelopes until the end of the study.

### Implementation {16c}

Treatment will be administered by a physical therapist who has sufficient experience and knowledge to perform it (NH).

## Assignment of interventions: blinding

### Who will be blinded {17a}

This study will be conducted as a double-blinded study. The patients, outcome assessor, and the statistician will be provided with information about the treatment process. However, they will remain unaware of the specific allocation throughout the study.

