### Trial design {8}

The current project is a double-blind 1:1 randomized controlled trial study designed to investigate and compare the effects of aerobic exercises and CPT in two parallel groups: group A consisting of CPT plus sham aerobic exercise and group B consisting of aerobic exercise and sham CPT. This study will be conducted at the CF specialized clinic of the Children’s Medical Center Hospital, Tehran, Iran; children and adolescents with confirmed diagnoses of CF will be randomly allocated to either group A or B.

Primary data points including FEV1, 6MWT, and secondary outcomes including sputum culture test (key secondary), FVC, and CFQ-R quality of life questionnaire will be assessed before and after treatments. It is expected that both treatments will have meaningful effects on the aforementioned variables and if significant changes are observed due to aerobic exercises compared to CPT, clinically, aerobic exercises will be recommended among treatment priorities.

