### Composition of the data monitoring committee, its role and reporting structure {21a}

The data monitoring committee consists of two of the authors (MK and [name]), a lung specialist doctor ([name]), and the statistician who will double check and analyze data and documents systematically, every week after it is entered into the STATA software by the conductor (NH).

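### The statistician is declared unaware of allocation, but a statistician generated it and no described step keeps the list or the arm labels from the analyst

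*Protocol article*

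**What the plan says.** Four parts of the protocol article bear on this.

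- **Who will be blinded {17a}** names three parties: the patients, the outcome assessor and the statistician. All three are told about the treatment process, but "they will remain unaware of the specific allocation throughout the study".
- **Allocation concealment {16b}** says "The randomization process was done by a statistician" before the study began. The result is held in "sealed numbered envelopes, corresponding to the sequential number of each person entered into the study", and "the therapeutic intervention will be adjusted based on the letters inside the envelopes". The same section then says who does not know the letters: "The examiner and participants will be unaware of the letters inside the envelopes until the end of the study".
- **Trial design {8}** publishes what the group names mean: "group A consisting of CPT plus sham aerobic exercise and group B consisting of aerobic exercise and sham CPT". The Interventions section {11a} and the two group descriptions repeat this, and Sequence generation {16a} uses the same names, A and B, for the allocation.
- **Composition of the data monitoring committee {21a}** includes "the statistician who will double check and analyze data and documents systematically, every week", once the data have been entered into the statistical software. Frequency and plans for auditing trial conduct {23} repeats the weekly review.

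**The concern.** Someone who produces an allocation sequence knows it. If the person who produced it is also the one described as blinded, the statement in {17a} cannot be true of that person. If they are two people, the blinding still depends on the list staying away from the analyst and on the data file not showing treatment through its group labels. The article describes neither.

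At stake is the integrity of the analytic decisions made once data are visible. The main analysis depends on checks of the outcome data (Statistical methods {20a}), and further analyses may be added if they become necessary during the study (Methods for any additional analyses {20b}). Analyst blinding is meant to stop such decisions being taken in the knowledge of which treatment they favour. If it is not in place, the final paper would credit the trial with a safeguard it did not have.

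**Working it through.** No arithmetic applies. The point turns on who can know the allocation, so the check sets the sections side by side.

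1. **Who made the sequence?** A statistician, before the start of the study ({16b}).
2. **What is it keyed to?** Each participant's sequential entry number, through numbered envelopes ({16b}).
3. **What does it contain?** Letters that determine the intervention ({16b}). The groups are called A and B ({16a}), so these letters are very probably A and B, although {16b} does not say so.
4. **Are those names masked?** No. Trial design {8} and the intervention sections define them. No section describes replacing them with neutral codes before data review or analysis.
5. **Who is covered by the described safeguards?** Under {16b}, the examiner and the participants are kept from the letters. Under Procedure for unblinding if needed {17b}, allocation may not be revealed to the outcome assessor or the patients. The statistician appears in neither list. Only the statement in {17a} claims blinding for the statistician, and no procedure stands behind it.
6. **Who handles the data?** The physiotherapist who delivers treatment ({16c}), and therefore knows the allocation, enters the data; the statistician then reviews and analyses them weekly ({21a}, {23}). No masking step is described between entry and review.
7. **Is a second statistician described?** No. {16b} introduces a statistician, identified by a name that has been removed. {17a}, {21a} and {23} refer to the role without introducing anyone new.
8. **Can the list be linked to the records?** Data management {19} says that documents carry a coded ID. It does not say whether that ID is the envelope number.

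Steps 1 and 7, read in the ordinary way, put {16b} in conflict with {17a}. Steps 4 to 6 show that nothing else in the article secures the claim. Steps 3, 7 and 8 each leave a fact open, and these limit how far the conclusion can go.

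**The case against.** The best defence is that the article never says the two statisticians are the same person. {16b} identifies an individual, whereas the later sections name only a role, and the removed name prevents a check. A condensed article that mentions no second statistician does not prove there is none. Nor does any section say that the analysis file is labelled A and B: the letters are what the therapist uses to deliver treatment, and a masked group variable would be compatible with {17a}. The coding of that variable could well be set out in a full protocol or analysis plan that is not shown.

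These arguments stand, and they rule out three stronger readings that a reader might infer:

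- **That analyst blinding does not exist, whoever the analyst is.** This needs either one person in both roles or an analysis file labelled A and B. Neither is documented.
- **That the analyst knows all 30 allocations.** This also needs the coded ID in {19} to be linkable to the envelope number, which is not stated.
- **That the harm can be sized as an inflated false-positive rate from choosing among several tests.** Two-sided p-values do not change when the arm labels are swapped. An analyst working on masked codes could choose the smallest p-value just as easily, so such a figure measures flexible test choice and not loss of blinding.

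Two further limits are fair. What is done if a normality or variance check fails, and the imputation model, are matters for an analysis plan and are not counted against the article here. And {20b} plans no extra analyses and requires any that arise to be justified and reported under a separate heading, which gives some protection.

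The defence does not remove the conflict between {16b} and {17a}. This is a property that the article states and that its own account of randomisation contradicts on a plain reading, so it is more than detail left to another document.

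**Conclusion.** The stated blinding of the statistician is inconsistent with Allocation concealment {16b} on its ordinary reading and is not secured by any procedure the article describes. The conclusion rests on the natural reading that the statistician mentioned later is the one already introduced, and on the absence of any described separation of roles or masking of labels.

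No number can be put on it. How many allocations the analyst knows depends on facts the article does not give, and no effect on the error rate can be derived. Patient and outcome-assessor blinding rests on separate provisions and is unaffected. The matter is worth correcting because the claim would carry into the final report and the correction is cheap.

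**What to change.** Reconcile {16b}, {17a} and {21a} by stating whether the person who generated the list also reviews or analyses the data, and then take one of two routes:

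- **Keep the claim.** State that the list is held by someone with no part in data review or analysis, that the analyst has not seen it, and that the review and analysis files carry neutral codes (for example X and Y). The key stays closed until the planned ANCOVA and any added analyses have been fixed.
- **Withdraw the claim.** If the same statistician generated the list and analyses the data, remove the statistician from the blinded parties in {17a} and report the analysis as not blinded.

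The first route costs a short amendment and a recoded group variable. The second costs the blinded-statistician claim and needs no extra staff. Neither affects patients or sample size.
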